#### Participants

Participants will include a total of 24–36 trainers and 900 providers embedded within three distinct organizations (8–12trainers and 300 providers per organization). We will partner with three organizations or departments responsible for provision of HIV services, each of which has broad reach in HIV endemic regions and has a productive relationship with the South Africa International TTC. To be eligible for this protocol, partners must provide healthcare services to individuals in key populations either diagnosed with HIV or at heightened risk of HIV-related consequences (e.g., sex workers, inmates in correctional facilities, adolescent girls and young women). Each partner organization will nominate staff to receive SBIRT instruction from the South Africa International TTC and to become certified SBIRT trainers. To be selected as an SBIRT trainer, individuals must meet the following criteria: (a) be currently registered with a regulatory body relevant to HIV care (e.g., registered counselor, nurse, medical doctor, psychologist, social worker); (b) have been with their current organization for at least 1 year; and (c) have experience providing training and/or supervision to direct front-line treatment providers. Following nomination by their organization, the South Africa International TTC team will conduct a brief screen to confirm eligibility.

At each organization, the 8–12 SBIRT trainers will in turn roll-out the curriculum to a minimum of 300 providers (average training size = 25–30 participants), thereby reaching approximately 900 providers in Years 2–4 (300 providers per organization * 3 organizations = 900 providers). Providers selected to receive the training will include the full range of treatment providers whom our partner organizations seek to train in effective alcohol screening and brief intervention. Based on our initial needs assessment, we expect our training attendees to be predominantly (approximately 70%) lay workers, with some representation of registered counselors, nurses, doctors, psychologists, and social workers. We also expect the demographics of the behavioral health workforce (both trainers and providers) to generally mirror the composition of the South African population, as reflected in the most recent census: Black African (80.2%), White (8.4%), Coloured—a South African census term for a multiracial ethnic group—(8.8%), Indian (2.5%), and Other/Unspecified (0.5%; [52]).

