##### Ongoing monitoring and consultation

Ongoing support will be offered for both the SBIRT trainers and the providers in the form of periodic live observation and ongoing consultation calls. For certified SBIRT trainers, the South Africa International TTC team will go out into the field and live observe all of the scheduled SBIRT training sessions. The trainers will be informed in advance that their sessions will be observed as part of the ongoing monitoring process. Using the same protocol as the role play sessions, the observer will live code the training sessions using the fidelity coding system. The observer will provide private feedback at the end of these training sessions on training delivery in terms of both adherence and skill.

For providers, the South Africa International TTC will hold hourly videoconference consultation calls the last week of each month every day of the work week (i.e., five calls per month). The agenda and curriculum for these calls was described in Phase 1. Because SBIRT training rollout will be staggered and calls will be optional, attendance is expected to be manageable. More frequent sessions will be offered if attendance consistently exceeds more than 25 training recipients per call. Both attendance and engagement in these calls will be tracked as indicators of engagement in the train-the-trainer curriculum.

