### Measures

Prior to the start of training activities, leaders at each partner organization will fill out an Organizational Background Form that will contain data about key contextual factors that might be relevant to implementation including provinces served, key populations served, patient census, number of providers employed, and specific HIV services provided.

Once training activities commence, data will be collected from trainers, providers, and from case report forms capturing patient encounter data. The timeline of measure administration for the trainer-, provider-, and patient encounter-level data is shown in Table 2. For both trainers and providers, additional data collection will include basic socio-demographics including years of experience in the field, years of employment at the organization, biological sex, gender, South African population group (e.g., the equivalent of race/ethnicity in the United States), and education.

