## Analysis plan

Aim 1 (creation of a Trainer Manual) will not require formal data analysis. For Aim 2, all SBIRT trainers (n = 24–36) and all providers who receive SBIRT training (minimum n = 900) will be included in the statistical analyses [57, 58]. Prior to the main analyses, we will run descriptive statistics on the outcomes collected as part of Aim 2 to examine distributional properties, identify outliers, and transform variables as needed. Missing data will be imputed following recommendations of the National Research Council [59]. We will test the appropriateness of assumptions underlying the use of multiple imputation using sensitivity analyses [60].

For Aim 2 evaluation of trainer outcomes, the proportion of training sessions that met the fidelity benchmark will be examined as an outcome of interest, with the goal that at least 80% will meet the target. In addition, we will examine pre-training to post-training change in trainer SBIRT knowledge and proportion of trainers who attained the 70% knowledge benchmark immediately at the culmination of training.

For Aim 2 evaluation of provider- and patient encounter-level variables, change in each outcome will be examined over three distinct time intervals: 3-months pre-training to training (i.e., baseline reports of the past 90 days); training to 3-months post-training; and 3- to 6-months post-training. We will use longitudinal models to examine whether the provider- and patient encounter-level implementation outcomes significantly change across 3 assessments. Repeated measures and nested structures (due to providers being nested within trainers) will be accounted for by adding appropriate random effect terms. The longitudinal models will be estimated using generalized estimation equations which lead to robust standard error and statistical inferences [61]. Using the models, we will examine the outcomes of each post-training visit and compare them with the pre-training outcome. An omnibus test also will be conducted to compare all post-training visit outcomes with the pre-training outcomes. In addition to reporting statistical significance, we will report the effect size using Cohen’s d [62].

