For Aim 3 exploratory analyses, we will test a series of multilevel models in which patient encounters (Level 1) are nested in providers (Level 2) which are nested within trainers (Level 3). Consistent with Raudenbush and Bryk’s multilevel modeling strategy, the proportion of variance to be explained at each level will be examined as an initial step [63]. Next, following a decomposed-first strategy that advocates for starting with moderation-focused hypotheses to avoid biases associated with conflated effects, we will conduct multilevel regressions testing the extent to which any putative covariates significantly moderate the hypothesized relationship among the variables [64]. We will test putative covariates (e.g., years of experience, biological sex, population group) at two levels: trainer and provider. All tests of moderation will adjust for the multi-level nature of the nested variables. If moderation is not found (e.g., if biological sex of the trainer does not moderate the effect of fidelity on provider attitudes), covariates will be controlled for as predictors. The goal of these analyses will be to determine the proportion of variance in patient encounter-level outcomes accounted for provider-level outcomes, and the proportion of variance in provider-level outcomes accounted for by trainer-level outcomes, after controlling for putative covariates. These data will help to elucidate mechanisms of action underlying the train-the-trainer cascading model.

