## Discussion

This protocol is designed to gather comprehensive data on multi-level factors associated with the implementation of SBIRT in HIV care settings throughout South Africa. Building upon the scaffolding and collaborative networks established by the South Africa International TTC, the proposed study will enable us to first codify and then evaluate an SBIRT train-the-trainer cascade model on implementation outcomes at multiple levels—trainer-level (i.e., knowledge, fidelity), provider-level (i.e., attitudes, confidence, acceptability), and patient encounter-level (i.e., reach of SBIRT to eligible patients).

It will be important in carrying out this protocol that operations are able to be readily adapted across a broad range of clinical and community care environments for individuals dually at risk for HIV and problem alcohol use, and as challenges arise. For example, this protocol will require work across a range of environments for training and intervention delivery, and there will likely be differences across organizations and units within organizations in familiarity with and access to technology. Further, as the COVID-19 pandemic continues to evolve, there will likely be need for more remote rather than in-person interactions as initially planned. Accordingly, the South Africa International TTC will develop the master training manual for both face-to-face and virtual delivery to ensure maximum flexibility. Any other adjustments made in response to the COVID-19 pandemic will be documented on an ongoing basis.

Findings from the research described in this protocol will be subject to important limitations. First, due to the lack of an integrated medical record system for consistent tracking both within and across our partner organizations, we will not be able to obtain true patient-level data. Instead, we rely on patient encounter-level data captured in real time using case report forms. The real-time nature of data collection will bolster confidence in data accuracy, but the data collected will only be as strong as the data entered, and may be subject to limitations as a result of both organization and provider adherence with the protocols. Second, while we are striving to work across a wide range of clinical and community care environments, and in a wide range of geographic locations, our data may not be generalizable beyond our partner organizations.

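### The Aim 3 multilevel model stops at the trainer, so most of any difference between the three organizations is counted as trainer variance and can confound trainer-level associations

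*Protocol article*

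**What the plan says.** The Analysis plan section of the protocol article sets out Aim 3 as a series of multilevel models in which "patient encounters (Level 1) are nested in providers (Level 2) which are nested within trainers (Level 3". The trainer is the top level. The first step is a partition of variance: "the proportion of variance to be explained at each level will be examined as an initial step". Covariates follow: "We will test putative covariates (e.g., years of experience, biological sex, population group) at two levels: trainer and provider". The stated goal is to find how much of the variation in encounter outcomes is explained by provider outcomes, and how much of the variation in provider outcomes is explained by trainer outcomes. The results are to be read as evidence on how the cascade model works.

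The Participants section describes trainers and providers "embedded within three distinct organizations", with 8–12 trainers and 300 providers in each. Each organization nominates its own trainers, who then train providers there. Before training starts, leaders complete an Organizational Background Form on "key contextual factors that might be relevant to implementation including provinces served, key populations served". The Discussion expects familiarity with technology, and access to it, to differ between organizations. The Analysis plan does not mention organization or give a use for the form.

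**The concern.** The design has a grouping above the trainer that the model leaves out. Trainers in one organization share an employer, a setting and working conditions. If provider outcomes differ between organizations for those reasons, trainers from different organizations will appear to differ from one another even if they train equally well. A model with the trainer on top has nowhere else to put that variation.

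Two Aim 3 results are exposed. One is the share of variance attributed to trainers, which is the first thing the plan looks at. The other is the association between trainer outcomes, such as fidelity, and provider outcomes. If both differ by organization, they can be correlated across the 24–36 trainers with no association among trainers in the same organization. A reader would then credit trainer quality with something that belongs to the organization.

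**Working it through.** **Inputs from the document.** There are three organizations with m = 8 to 12 trainers each, so k = 3m = 24 to 36 trainers (Participants). The trainer is the top level (Analysis plan, Aim 3). The document gives no organization variance and no figure of its own on this point to reproduce, so every variance below is an assumption.

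**Step 1: where organization variance goes.** Let vt be the true trainer variance within organization and vo the organization variance. With organization ignored, the expected variance among the k trainer effects is

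vt + vo × [1 − (m − 1)/(3m − 1)] = vt + vo × 2m/(3m − 1).

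The multiplier of vo depends only on the design:

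- m = 8 (k = 24): 16/23 = 0.696
- m = 10 (k = 30): 20/29 = 0.690
- m = 12 (k = 36): 24/35 = 0.686

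About 69% of the organization variance is therefore reported as trainer variance.

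**Step 2: what that does to the trainer component.** Take m = 10, total variance 1 and true trainer variance 0.05:

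| Assumed vo | Apparent trainer variance | Part due to organization |
|---|---|---|
| 0.02 | 0.05 + 0.690 × 0.02 = 0.064 | 22% |
| 0.05 | 0.05 + 0.690 × 0.05 = 0.085 | 41% |
| 0.10 | 0.05 + 0.690 × 0.10 = 0.119 | 58% |

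With no true trainer variance and vo = 0.05, the apparent value is still about 0.034. Simulation with 30 providers per trainer agrees: 0.085 for vo = 0.05 and 0.116 for vo = 0.10 (both with vt = 0.05), and 0.033 for vt = 0. Estimating trainer variance within organization returned 0.050, 0.050 and 0.000.

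**Step 3: false associations at trainer level.** A trainer-level predictor and outcome were simulated with no association within organization, and organization explained the same share of each. The table gives the rejection rate of a two-sided 5% slope test that ignores organization:

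| Organization share in both | 24 trainers | 36 trainers |
|---|---|---|
| 5% | 5.1% | 4.9% |
| 10% | 5.3% | 5.8% |
| 20% | 7.0% | 8.3% |
| 30% | 9.6% | 12.3% |
| 50% | 19.5% | 25.8% |

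The first three rows use 40,000 runs and the last two use 6,000. Repeat runs agreed to about half a percentage point, so the ranges quoted elsewhere in this point are rounded (7–9% at a 20% share). At shares of 30% and 50%, organization fixed effects brought the rate to 4.5–5.2%.

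**The case against.** The strongest reply is that the text does not exclude organization. The covariate list gives examples only. Organization is constant within a trainer, so an organization indicator is formally a trainer-level covariate that could be adjusted for under the plan as written. This stands in part: the fix fits within the plan's framework. It does not remove the point. Organization is not named, and the levels are spelled out without it. The variance partition is also described as the initial step, before any covariate enters, so a covariate added later would not correct it.

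A second reply is that the effect may be small. All trainers are taught by one center and must reach the same role-play benchmark before certification, which may limit organization differences in fidelity. The table shows almost no inflation at shares of 5–10%, and Aim 3 is labelled exploratory. All of this stands, and it limits how serious the point is.

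Three stronger readings are tempting, and the document does not support them.

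- **Aim 2 is biased in the same way.** The Aim 2 text also names only one nesting: "Repeated measures and nested structures (due to providers being nested within trainers) will be accounted for by adding appropriate random effect terms". But a stable organization difference cancels from a within-provider change, so an organization main effect would remove no bias from the pre-post contrast.
- **A calendar-quarter term would separate training from secular change.** A reader might infer this from "Because SBIRT training rollout will be staggered and calls will be optional" and from the remark "as the COVID-19 pandemic continues to evolve". Each provider contributes three consecutive three-month intervals, so interval and quarter advance together. With cohort or provider effects the design is rank-deficient by one. A linear training trend and a linear secular trend can be separated only by assuming that early and late cohorts are exchangeable. Nor does the document say that every record is dated: the listed encounter fields include no date, and the pre-training data are reports covering the previous 90 days.
- **The partners serve different populations.** The background form records the populations served, but nothing states that they differ between the three partners. The stated expectation concerns technology.

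**Conclusion.** The point holds for Aim 3 only. That about 69% of any organization variance passes into the trainer component follows from the design and needs no assumption beyond equal numbers of trainers per organization. How much this matters depends on organization variance, which is unknown. About 41% of the apparent trainer variance would be organizational if organization and trainer variances were equal. The false-positive rate of a trainer-level slope runs from close to nominal at small organization shares to about one in four at a 50% share with 36 trainers. Those rates assume equal shares in predictor and outcome. Because the variance shares are a declared product of Aim 3, the correction is worth making, but the exploratory status of the aim keeps this a modest point.

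**What to change.** Add organization as a fixed effect to all Aim 3 models, including the initial variance partition. State that trainer variance and trainer-level slopes are reported within organization. With only three organizations a fixed effect is the workable form, since a fourth-level random variance would be estimated on 2 degrees of freedom.

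The change is one of analysis wording. Organization membership is known by design, so no new data are needed. The cost is 2 degrees of freedom out of 24–36 trainers: for a single trainer-level slope, the residual degrees of freedom fall from 22–34 (k − 2) to 20–32 (k − 4). Trainer variance also becomes a within-organization quantity and no longer describes variation across the whole set of trainers, and the report should say so. No change to the Aim 2 models is called for on this ground.

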#### Patient encounter-level measures

To evaluate how SBIRT training impacts provider-patient encounters, we will measure data from all patient encounters in the participating units of organizations in real-time using brief session report forms. These forms will be collected via programmed tablets and/or scannable forms administered by providers to patients. Patient encounter-level data will include the patient’s gender, race, HIV status, and whether the patient is currently receiving HIV treatment.

Additional fields will include documentation of the AUDIT screening results. The first two fields will be used to indicate (1) whether or not the patient is screened for alcohol use (yes/no) and (2) scores for each of the 10 items on the AUDIT. When completed via tablet, the sum of AUDIT items contained in Question 2 will auto-calculate. When completed via paper, providers will be given a basic scoring template to calculate and interpret the score. A user-friendly table will be provided that summarizes the patient’s risk level and recommended intervention in accordance with the risk algorithm(modeled after Table 1), while the tablet will directly indicate which level of care is recommended. This will result in field (3) recommended action based on AUDIT (which will either be automated on the tablet or clearly noted on the paper forms based on score), and then the provider can enter field (4) final action taken (no action taken, positive feedback / encouragement about drinking given, brief intervention provided, or brief intervention provided with referral to specialty care). Data collected using these fields will be used to assess a patient encounter-level measure of reach, calculated as the proportion of total patient encounters over the specified recall time period during which the patient received screening, brief intervention, and referral to treatment.

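### Aim 3 limits covariates to trainer and provider level, so patient mix, although recorded at each encounter, stays in the between-provider variance

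*Protocol article*

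**What the plan says.** The Analysis plan sets up the Aim 3 models with encounters at Level 1, providers at Level 2 and trainers at Level 3. On covariates it states: "We will test putative covariates (e.g., years of experience, biological sex, population group) at two levels: trainer and provider". A covariate that does not moderate is kept as a control. The goal is "the proportion of variance in patient encounter-level outcomes accounted for provider-level outcomes", together with the matching share for trainer-level on provider-level outcomes, "after controlling for putative covariates".

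The section on patient encounter-level measures states: "Patient encounter-level data will include the patient’s gender, race, HIV status, and whether the patient is currently receiving HIV treatment". None of these fields appears in the Analysis plan. The same section defines reach for screening, brief intervention and referral as "calculated as the proportion of total patient encounters over the specified recall time period". Table 1 ties brief intervention to AUDIT scores of 8 and above and referral to scores of 20 and above.

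Under Participants, the populations that a partner organization may serve include "sex workers, inmates in correctional facilities, adolescent girls and young women". The section on power says that 900 providers should suffice for moderator effects in provider-level and encounter-level data.

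**The concern.** An encounter outcome depends on the patient as well as on the provider. For brief intervention and referral this is built in: the recommended action follows the patient's AUDIT zone, and the denominator is all encounters. A provider who sees few at-risk patients will show low rates whatever their attitude or confidence. For screening, patient mix matters if the chance of being screened varies with patient characteristics.

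With no patient covariate in the model, such differences become part of the between-provider variance. If attitudes or confidence happen to correlate with patient mix, part of that variance is also attributed to them. Variance shares are what Aim 3 sets out to report, and the plan intends to read mechanisms of the training cascade from them. The plan also chooses a decomposed-first strategy in order to avoid conflated effects. Leaving out the Level 1 patient factors works against that intention.

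**Working it through.** The plan states no figure on this point, so there is none to reproduce. The check has three parts.

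**1. The text.** The encounter is a level of the model. Four patient fields exist at that level. The sentence on covariates names two levels and omits this one. The *e.g.* in that sentence leaves the list of covariates open but not the levels. Controlling for covariates therefore means controlling at trainer and provider level. No other section enters a patient characteristic in a model, and the limitations in the Discussion do not mention patient mix.

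**2. Between-provider variance.** Take one binary patient factor with odds ratio OR, whose share in the caseload has standard deviation s across providers. On the logit scale it adds (ln OR × s)² to the true between-provider variance τ². The fraction that is only patient mix is (ln OR × s)² / [(ln OR × s)² + τ²]. All inputs are assumed: OR 1.5 to 3, s 0.1 to 0.3, τ² 0.1 to 0.5.

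- Lowest: (0.405 × 0.1)² = 0.0016. With τ² = 0.5 the fraction is 0.0016 / 0.5016 = 0.3%.
- Highest: (1.099 × 0.3)² = 0.1086. With τ² = 0.1 the fraction is 0.1086 / 0.2086 = 52%.
- By τ²: 1.6% to 52% at 0.1, 0.5% to 27% at 0.3, and 0.3% to 18% at 0.5.

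This part needs no correlation between patient mix and any provider score.

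**3. Credit to a provider score.** A simulation used 900 providers (from the plan) and, as assumptions, 100 encounters each, τ² = 0.3, and a patient-factor share varying with standard deviation 1 on the logit scale. The provider score has no true effect and correlates r with patient mix. Provider rates were regressed on the score, with and without removal of the patient factor, in 400 runs per setting.

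| OR | r | False positives, unadjusted | Adjusted | R², unadjusted | Adjusted |
|---|---|---|---|---|---|
| 1.5 | 0 | 5.8% | 6.2% | 0.001 | 0.001 |
| 1.5 | 0.2 | 15.0% | 3.5% | 0.002 | 0.001 |
| 1.5 | 0.4 | 38.8% | 3.5% | 0.004 | 0.001 |
| 2 | 0 | 6.8% | 6.0% | 0.001 | 0.001 |
| 2 | 0.2 | 27.3% | 4.0% | 0.003 | 0.001 |
| 2 | 0.4 | 80.7% | 5.8% | 0.010 | 0.001 |
| 3 | 0 | 4.8% | 3.5% | 0.001 | 0.001 |
| 3 | 0.2 | 56.5% | 6.8% | 0.006 | 0.001 |
| 3 | 0.4 | 99.5% | 4.8% | 0.022 | 0.001 |

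The Monte Carlo standard error near 5% is √(0.05 × 0.95 / 400) = 1.1 percentage points, so the r = 0 rows and the adjusted column are compatible with the nominal 5%. The R² expected by chance alone is 1/899 = 0.001. With OR = 1, unadjusted rates were 4.8% to 6.2% at every r. Inflation therefore needs both a patient effect and a correlation. The simulation works on provider rates and has no trainer level, so it shows direction and rough size only.

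**The case against.** Several points on the other side carry weight.

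- **Exploratory aim in a condensed article.** The covariate list is open, and its full content may stand elsewhere. This lowers the weight of the point. It does not remove it, because the levels are stated and not merely left unspecified.
- **The power section mentions encounter-level data.** One may read this as encounter-level moderators being intended. It may equally mean moderators of encounter-level outcomes. The wording does not settle the matter.
- **The bias is conditional.** A reader might infer that patient mix will be credited to providers and that the conclusions on mechanism will be wrong. The documents do not support this: nothing in them says that attitudes or confidence correlate with patient mix, and at r = 0 there is no inflation.
- **The plan's own metric moves little.** Aim 3 reports shares of variance, and the spurious R² is at most about 2 percentage points in the settings tried. This stands. The false-positive rates are high because 900 providers make even a small R² significant.
- **Caseload differences are not documented.** A reader might infer from the listed key populations that caseloads differ strongly between providers. The list illustrates which partners are eligible and says nothing about variation between providers within a partner.
- **AUDIT risk might seem to be handled already.** The Discussion speaks of reach to eligible patients, which could suggest a denominator restricted by AUDIT zone. The measure as defined uses total encounters, so no such safeguard exists.
- **Over-adjustment.** Providers complete the forms. If attitudes influence which encounters or fields are recorded, the recorded mix is partly a consequence of the exposure. This is a fair warning, and it is why both sets of results should be shown.

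**Conclusion.** The point holds as a stated restriction that leaves recorded patient characteristics out of the Aim 3 encounter-outcome models. Differences in patient mix then stay in the between-provider variance for all three encounter outcomes, to the extent that each depends on the patient. They can be attributed to provider attitudes or confidence if these correlate with the mix.

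The size cannot be derived from the documents. Every odds ratio, standard deviation, variance and correlation used above is an assumption. Within those ranges, false-positive rates run from nominal to far above it, and the spurious R² in the correlated settings is 0.002 to 0.022.

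The weight is low to moderate. Aim 3 is exploratory, Aim 2 does not rest on it, and the trainer-to-provider models have no encounter-level outcome and are not affected. Adjustment for the four fields would also be partial. They do not replace AUDIT risk, which is known only for screened patients and so cannot serve the screening outcome.

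**What to change.** In the Aim 3 encounter-outcome models, allow covariates at three levels. Enter patient gender, race, HIV status and current HIV treatment at Level 1 and their provider means at Level 2. The provider means are needed because patient covariates centred within provider do not by themselves adjust a provider-level predictor. Report the variance shares with and without this adjustment.

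Reconcile the covariate sentence in the Analysis plan with the moderator wording in the power section, so that it is clear whether encounter-level moderators are meant.

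The variables are already collected, so nothing changes in conduct or sample size. The cost is some extra analysis and the need to deal with missing or selectively recorded patient fields. Showing both sets of results lets the reader judge possible over-adjustment.
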